## Abstract

**Introduction:** Ischemic and hemorrhagic strokes in the brainstem and cerebellum with injury to the functional loop of the Guillain-Mollaret triangle (GMT) can trigger a series of events that result in secondary trans-synaptic neurodegeneration of the inferior olivary nucleus. In an unknown percentage of patients, this leads to a condition called hypertrophic olivary degeneration (HOD). Characteristic clinical symptoms of HOD progress slowly over months and consist of a rhythmic palatal tremor, vertical pendular nystagmus, and Holmes tremor of the upper limbs. Diffusion Tensor Imaging (DTI) with tractography is a promising method to identify functional pathway lesions along the cerebello-thalamo-cortical connectivity and to generate a deeper understanding of the HOD pathophysiology. The incidence of HOD development following stroke and the timeline of clinical symptoms have not yet been determined in prospective studies—a prerequisite for the surveillance of patients at risk.

**Methods and Analysis:** Patients with ischemic and hemorrhagic strokes in the brainstem and cerebellum with a topo-anatomical relation to the GMT are recruited within certified stroke units of the Interdisciplinary Neurovascular Network of the Rhine-Main. Matching lesions are identified using a predefined MRI template. Eligible patients are prospectively followed up and present at 4 and 8 months after the index event. During study visits, a clinical neurological examination and brain MRI, including high-resolution T2-, proton-density-weighted imaging, and DTI tractography, are performed. Fiberoptic endoscopic evaluation of swallowing is optional if palatal tremor is encountered.

**Study Outcomes:** The primary endpoint of this prospective clinical multicenter study is to determine the frequency of radiological HOD development in patients with a posterior fossa stroke affecting the GMT at 8 months after the index event. Secondary endpoints are identification of (1) the timeline and relevance of clinical symptoms, (2) lesion localizations more prone to HOD occurrence, and (3) the best MR-imaging regimen for HOD identification. Additionally, (4) DTI tractography data are used to analyze individual pathway lesions. The aim is to contribute to the epidemiological and pathophysiological understanding of HOD and hereby facilitate future research on therapeutic and prophylactic measures.

**Clinical Trial Registration:** HOD-IS is a registered trial at https://www.drks.de/drks_web/navigate.do?navigationId=trial.HTML&TRIAL_ID=DRKS00020549.

## Introduction

Stroke is characterized by the sudden onset of a focal neurological deficit with complete or incomplete recovery over time. Some patients with infratentorial strokes, however, develop a novel clinical worsening months after the index event and with considerable impairment to their daily routine. The occurring syndrome consists of a palatal tremor (PT), vertical pendular nystagmus, and (dentatorubral) Holmes tremor of the upper limbs. This is attributed to a phenomenon called hypertrophic olivary degeneration (HOD) in which lesions to the anatomical-functional brainstem loop of the Guillain-Mollaret triangle (GMT) lead to a spatially distant degeneration of the inferior olivary nucleus (1, 2). The GMT has a unidirectional orientation of inhibitory fibers and is composed of three anatomic structures: the red nucleus (RN) in the mesencephalon, the ipsilateral inferior olivary nucleus (ION) in the medulla, and the contralateral dentate nucleus (DN) of the cerebellum (Figure 1) (3–6). It is also referred to as the dentato-rubro-olivary pathway (DROP) (7). The radiological MRI diagnosis of HOD is based on the finding of a circumscribed ION hyperintensity on T2-weighted sequences within 1 to 12 months after the index event—additional olivary hypertrophy usually after 12 months is optional (4, 8, 9).

**Figure 1 F1:**
[figure not shown]
The Guillain–Mollaret triangle (GMT) (blue) and its unidirectional course of inhibitory fibers, which ascend from the dentate nucleus (DN) to the contralateral red nucleus (RN) and then descend ipsilaterally to the inferior olivary nucleus (ION). The bilateral overlapping Guillain–Mollaret triangles together form a “tilted star of David configuration” (5). Fibers of the GMT, which is also called the dentato–rubro–olivary-pathway, overlap with dentato–thalamo–cortical pathways proceeding into both hemispheres (black arrow) (10). HOD, hypertrophic olivary degeneration; SCP, superior cerebellar peduncle; ICP, inferior cerebellar peduncle; RN, red nucleus; CTT, central tegmental tract; DN, dentate nucleus; ION, inferior olivary nucleus.

Regularly, strategic brain infarcts and intracerebral hemorrhages in the posterior fossa set lesion to the GMT and initiate a cascade of trans-synaptic events, which ultimately results in HOD (10) (Figure 2). Disinhibition of the ION leads to cerebellar malfunction and the establishment of clinical symptoms in the fine motor and pharyngeal system. Though HOD has been known for over a century, epidemiological knowledge has hardly progressed since, and neither larger clinical analyses nor prospective data are available (11, 12). A causal therapy of HOD development does not exist, and there is very limited evidence for symptomatic medical options (10, 13).

Advanced imaging techniques have been sporadically applied in HOD patients in this regard to visualize fiber tracts associated with HOD development. Diffusion tensor imaging (DTI) with tractography can be used to analyze the change in fiber tract volume following injury in the GMT (14–16). The use of this method systematically to investigate the HOD development and more precisely understand the injury to brainstem connectivity is promising beyond merely pinpointing down a lesion to an anatomic localization on MRI or in *ex-vivo* pathological studies. Furthermore, the distinction between affected and unaffected patients allows us to identify contributing factors to HOD occurrence. To our knowledge, no such prospective acquisition of DTI fiber tracking data in HOD patients has been described in the literature so far.

Moreover, proton density (PD)-weighted imaging was shown to be well-suited for detecting infratentorial lesions in the posterior fossa, yielding good contrast between cerebrospinal fluid (CSF) and brainstem lesions (17, 18). Transferring this to HOD imaging, it can be hypothesized that double-echo sequences (including T2- and PD-weighted datasets) are superior in the detection of HOD compared to conventional T2-weighted imaging and provide an improved detectability of the underlying lesion to the GMT.

### Objective

This study is designed to prospectively determine the frequency of HOD following ischemic or hemorrhagic lesions in the Guillain-Mollaret triangle and to examine the development of the associated clinical syndrome. As a secondary goal, the implementation of advanced imaging methods, comprising DTI for fiber tractography, will be prospectively applied to correlate the clinical findings over time with the respective fiber tract injury and generate a pathophysiological timeline of HOD development. Furthermore, the patient cohort is well-suited to compare the detectability of radiological HOD in T2- and PD-weighted data.

## Methods and Analysis

### Design

This is a prospective multicenter study conducted in Hesse, Germany, with a 2-year-recruitment period from March 2020 to February 2022. Patients with cerebral infarctions and cerebral hemorrhages in the brainstem and cerebellum with a topo-anatomical relation to the GMT are included and followed prospectively for 8 months (Figure 3). The patients are exclusively selected based on a pre-defined digital MRI template covering the region of interest (Figure 4). During this period, two clinical neurological examinations and two follow-up MRI scans of the brain are performed at 4 and 8 months after the index event, respectively. Three major targets are defined: (1) determining the risk of HOD development for patients with ischemic or hemorrhagic lesions within the GMT, (2) defining the timeline of radiological and clinical onset of HOD, and (3) defining a real-world pattern of the clinical syndrome of HOD in clinical follow-up examinations. Three secondary targets are defined: (a) the acquisition of an additional MRI DTI protocol with fiber tractography to demonstrate the chronological decrease in fiber tract volume over time in parallel to the development of clinical symptoms and conventional radiological findings, (b) the acquisition of MRI double-echo PD-/T2-weighted images to analyze the best detectability of radiological HOD in comparison to conventional T2-weighted sequences, and (c) the assessment of PT associated dysphagia by a follow-up examination by speech therapists with Fiberoptic endoscopic evaluation of swallowing (FEES) (Figure 5) (19). The study does not include medication or the admission of computed tomography (CT) or other sources of radiation at any point.

**Figure 3 F3:**
[figure not shown]
Study design chart of the HOD-IS trial.

**Figure 4 F4:**
[figure not shown]
Excerpt of the study brochure, which shows an MRI template with the regions of interest.

**Figure 5 F5:**
[figure not shown]
Fiberoptic endoscopic footage (FEES) of two patients **(A,B)** with HOD and dysphagia who showed involuntary movements of the soft palate and pharynx due to rhythmic contraction of the levator veli palatine, so-called palatal tremor (images used with permission from Dr. medic. [name], Frankfurt).

### Sample Size

Due to the exploratory study design, an exact power calculation is not feasible. For the purpose of this study—the determination of HOD frequency after posterior fossa stroke—a maximum 10% deviation of actual disease incidence is considered within acceptable boundaries. Therefore, it is calculated that with a targeted study size of 100 study subjects, the 95% confidence limits are ≤ 10% different (absolutely) from the estimated cumulative frequency of HOD occurrence (e.g., if 30 cases are detected in *n* = 100 subjects, the 95% confidence limits are thus 0.21 and 0.40, as calculated by the Clopper-Pearson Exact method). A minimum of *n* = 100 patients is thus the targeted sample size. In addition, empirical data in the recruiting centers were assessed to approximate if sufficient patients matching inclusion criteria could be recruited. Based on yearly benchmark reports derived from the local quality assurance registry (https://www.gqhnet.de/leistungsbereiche/schlaganfall), ~6,000 ischemic and hemorrhagic stroke patients can be expected in the recruiting stroke centers per year (see below). A detailed evaluation of consecutive stroke patients from the Lausanne Stroke Registry showed that among 1,000 patients with first-ever stroke, 113 isolated brain stem infarctions, 17 isolated cerebellar infarctions, seven isolated brain stem hemorrhages, and nine isolated cerebellar hemorrhages can be expected (20). Other studies confirmed this distribution (21). Applying these numbers to the local prerequisites, an equivalent of 1,927 strokes in the brainstem and cerebellum in the 2-year study period can be estimated for the recruiting centers. Additionally, the study templates with the regions of interest were applied on 40 consecutive brainstem and cerebellar strokes in a pilot run in 2018, which showed that 35% of strokes had a general topo-anatomical relation to the GMT. Thus, in a 2-year period, 674 stroke patients with lesions affecting the region of interest can be expected in the recruiting centers. However, strict application of exclusion criteria showed that only a smaller portion of those patients could have been recruited, especially due to a lack of MR-feasibility, missing patient consent, and progressed disability due to the index stroke and advanced patient age (reflected in mRS > 4). Moreover, the SARS-Covid-19 pandemic unforeseeably complicates recruitment. Hence, the targeted number of patients to include in this study is *n* = 100, leaving a necessarily large scope for expected recruitment failures and patient exclusions. Based on these 100 patients, the proportion of patients developing HOD as well as the timeline of HOD development will be determined.

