## Discussion

This is the first prospective study aimed to determine the incidence of HOD following ischemic and hemorrhagic stroke with injury inflicted to the GMT. Furthermore, clinical and pathophysiological aspects of HOD will be assessed as secondary targets.

The development and clinical application of a region-of-interest template and identification of lesions in the GMT more prone to cause HOD is a key component of the study. In order to prevent a selection bias and include patients as objectively as possible, the radiological template for patient recruitment is designed to be generous in size around key structures of the GMT. Therefore, also patients with partial or minor affection of GMT structures can be included in the study, allowing for a more differentiated analysis.

In this study, brain MRI is performed at two fixed time points after the index event, which allows us to determine the disease incidence and duration until HOD visibility. Due to the nature of the study, the timestamps of study visits are set arbitrarily, and no statement is possible to distinguish HOD occurrence before or in between study visits. However, 4 and 8 months were chosen based on the expected time course of HOD based on a meta-analysis of literature (4). During the drafting of this exploratory study, it was hypothesized that an estimate of 20% of patients with a plausible lesion to the GMT will have developed HOD on MRI 8 months after the index event. This is, however, based solely on small, retrospective data and is open to be proven otherwise by the results (3, 10).

Moreover, the influence of the specific lesion location in the GMT on the probability of HOD development is still unknown. This study aims to investigate whether the effect of structures such as the DN, central tegmental tract, or RN is associated with an increased risk of HOD compared to other localizations. Knowledge of a specific incidence based on lesion location justifies a prospective follow-up of stroke patients at risk of developing HOD. Though no treatment or prophylaxis for HOD exists yet, in the future, prospective therapeutic measures could be explored, such as inhibiting the excitatory fiber tracts involved in HOD development by medicinal GABAergic modulation.

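### The claim that 100 subjects give 95% limits within 10 points holds only for 30 or fewer, or 70 or more, cases, and has no allowance for patients lost before the 8-month MRI

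*Protocol article*

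**What the plan says.** Interval width is the only statistical basis that the Sample Size section gives for the number 100; the rest of the section concerns whether enough patients can be found. The section sets the tolerance ("a maximum 10% deviation of actual disease incidence is considered within acceptable boundaries") and then asserts that with 100 subjects "the 95% confidence limits are ≤ 10% different (absolutely) from the estimated cumulative frequency of HOD occurrence". The illustration is 30 cases in 100, for which "the 95% confidence limits are thus 0.21 and 0.40, as calculated by the Clopper-Pearson Exact method".

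The same section calls 100 a minimum. It later fixes it as an inclusion figure ("Hence, the targeted number of patients to include in this study is" 100) and says that the proportion with HOD will be determined on these 100 patients.

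Under Inclusion and Exclusion Criteria, patients enter within 14 days of the stroke. Under Primary Endpoint, the outcome is read on an MRI 8 months after it. The Discussion gives the frequency that the investigators expected: "an estimate of 20% of patients with a plausible lesion to the GMT will have developed HOD on MRI 8 months after the index event".

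**The concern.** The statement is written as a property of the sample size, without reference to the frequency observed. The width of an exact binomial interval depends on both the frequency and the number analysed, and the statement fixes neither correctly. The example of 30 in 100 happens to lie at the last count below one half for which the 10-point limit is met. The number in the calculation is the number to be included, whereas the endpoint exists only for patients scanned at 8 months.

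Since the 10-point tolerance is what justifies the sample size, the final report could miss its own stated limit even if recruitment goes exactly to plan.

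**Working it through.** **Inputs.** From Sample Size: two-sided 95% Clopper-Pearson limits, a 10-point absolute tolerance, n = 100, and the 30% example. From the Discussion: the hypothesised 20%. Losses of 10 to 20% between inclusion and the 8-month MRI are my assumption, because the article states no rate.

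**Formula.** For x cases in n patients, the lower limit L is the 0.025 quantile of Beta(x, n − x + 1), and the upper limit U is the 0.975 quantile of Beta(x + 1, n − x). The distance to compare with 10 points is D = max(x/n − L, U − x/n).

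**The plan's own figure.** For 30/100, L = 0.2124 and U = 0.3998, which reproduces the stated 0.21 and 0.40. D = 0.3998 − 0.3000 = 9.98 points, so the slack is 0.02 points.

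**All 100 evaluable, other counts.**

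| Cases/n | 95% limits | D (points) |
|---|---|---|
| 20/100 | 0.1267 to 0.2918 | 9.18 |
| 30/100 | 0.2124 to 0.3998 | 9.98 |
| 31/100 | 0.2213 to 0.4103 | 10.03 |
| 50/100 | 0.3983 to 0.6017 | 10.17 |

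D exceeds 10 points for every count from 31 to 69. Its maximum is 10.29 points.

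**After losses, at 30%** (nearest whole count).

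| Cases/n | 95% limits | D (points) |
|---|---|---|
| 30/99 | 0.2147 to 0.4035 | 10.05 |
| 27/90 | 0.2079 to 0.4057 | 10.57 |
| 24/80 | 0.2026 to 0.4128 | 11.28 |

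One lost patient is enough to pass 10 points.

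**After losses, at 20%.**

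| Cases/n | 95% limits | D (points) |
|---|---|---|
| 18/90 | 0.1231 to 0.2975 | 9.75 |
| 17/86 | 0.1196 to 0.2975 | 9.98 |
| 17/85 | 0.1210 to 0.3008 | 10.08 |
| 16/80 | 0.1189 to 0.3044 | 10.44 |

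Here the limit is still met with 86 evaluable patients (14% lost) and is passed at 85 (15% lost).

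**Range for a restated claim.** For observed frequencies of 20 to 50%, D runs from 9.18 points (20/100) to 10.29 points with 100 evaluable patients, and from 10.44 points (16/80) to 11.57 points (33/80) with 80.

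**The case against.** The best defence is that the arithmetic shown is right and the excess is trivial. The example reproduces, and with 100 evaluable patients both frequencies named in the article satisfy the limit (9.18 points at 20%, 9.98 at 30%). The failure between 31 and 69 cases is at most 0.29 points, which disappears when rounded to whole percentage points. That settles the size of the problem. It does not make a general statement true, and the general statement is what supports the 100.

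On losses, 100 is called a minimum, and the sentence about determining the proportion on these 100 patients could be read as 100 analysed. The later sentence, however, makes 100 the number to include. The wide scope left for recruitment failures and exclusions is drawn from the 674 candidates and concerns the stage before inclusion, so it does not enlarge the 100. The four-week visit tolerance under Anticipated Outcomes and Limitations should reduce missed scans, but the same section expects the pandemic to limit imaging and visits. Its remark that 100 may be too few for an exact incidence is a fair general caveat and leaves the stated figure uncorrected.

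A condensed article may leave the handling of attrition to the full protocol. The missing loss rate is therefore not a fault in itself; the point rests on the numerical claim as printed.

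It also stands that the study calls itself exploratory, that no test or decision depends on the 10 points, and that the confidence interval will be reported, so readers will see the precision achieved.

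**Conclusion.** The point holds, as a minor one. The unconditional 10-point claim is untrue for 31 to 69 cases even with every included patient scanned, and at the article's 30% example it does not survive the loss of one patient.

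A reader might infer that the claim also fails at the 20% the investigators expected as soon as patients are lost. It does not: at 20% it holds up to about 14% loss. Nor do the documents support saying that the study will miss its precision under realistic losses, because they give no loss rate. Under an assumed 20% loss the excess is 0.4 points at 20% (16/80) and 1.3 points at 30% (24/80). Excesses of that size do not make the sample inadequate for estimating a frequency in an exploratory cohort.

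**What to change.** In Sample Size, tie the precision to patients with an evaluable 8-month MRI and drop the unconditional limit. Suggested wording: *With 80 to 100 patients evaluable at 8 months, the 95% Clopper-Pearson limits lie within about 9 to 11.6 percentage points of the estimate for frequencies of 20 to 50%.*

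Replace the 30% example with the hypothesised 20%, which also brings the section into line with the Discussion: 20/100 gives 0.127 to 0.292, and 16/80 gives 0.119 to 0.304. The range of 80 to 100 reflects an assumed loss of up to 20%. If the sponsor has its own estimate of loss, that should replace it.

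The cost is a slightly less favourable stated precision. No extra patients and no change to the analysis are needed.

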
### Selection of Subjects

Patients are recruited within certified stroke centers in Hesse, Germany, which are members of the Interdisciplinary Neurovascular Network of Rhine-Main (INVN, http://invn.de/), one of 16 neurovascular networks in Germany funded by the German Stroke Society (DSG). All clinics hold a DSG-certified stroke unit and special expertise in the diagnosis and treatment of cerebrovascular diseases and neurological rehabilitation. For patient selection, a study brochure is handed out to the cooperating centers and respective radiology departments with an MRI template of imaging hallmarks of the GMT lesions (Figure 4).

### Inclusion and Exclusion Criteria

Patients are eligible for this study if they are older than 18 years and present in the recruiting centers with an intracerebral hemorrhage or cerebral infarction in the brainstem or the cerebellum not older than 14 days with topo-anatomical relation to the GMT. The region of interest is evaluated on clinical MRI or CT and predefined by the study template (Figure 4). If there is a match of lesion localization and MRI template the patient will be asked by the respective study centers to participate in the study. If there is an agreement, baseline clinical data is anonymously recorded in the study database, and the patient is contacted for follow-up (Figure 3).

Written informed consent is mandatory for recruitment. Patients are excluded from the study if explicit consent to participate in the study cannot be given due to coma or lack of legal competence. Further exclusion criteria are visibility of new operative injury on MRI (e.g., after an occipital craniotomy), contraindications to perform MR-imaging (such as pacemakers, ferromagnetic materials in the body, and claustrophobia), age under 18 years, and a modified Rankin Scale (mRS) of more than four points, which precludes transportation.

### Study Outcomes

All patients are asked to undergo follow-up MR-imaging done at the Brain Imaging Center (BIC) of the Goethe University Frankfurt. Furthermore, at the time of study visits, a clinical neurological examination is performed by a study physician following a study exam catalog. The symptoms of a rhythmic PT, pendular nystagmus, and Holmes tremor of the upper limbs are specifically evaluated by a physician with experience in the field. A complete neurological exam is performed, including gait testing. The individual disability outcome is measured by the modified Rankin Scale (mRS) during each study visit. If PT is encountered, the patient is offered an evaluation of dysphagia by a speech-language pathologist, including optional FEES.

MRI examinations are performed on a 3T whole-body MRI scanner (MAGNETOM Prisma, Siemens Healthineers, Erlangen, Germany) using a body transmit and a 20-channel phased-array head/neck receive coil (Siemens Healthineers, Erlangen, Germany). As an anatomical reference, a T1-weighted data set with whole-brain coverage and an isotropic resolution of 1 mm are acquired using a 3D magnetization-prepared rapid-gradient-echo imaging (MP-RAGE) sequence (22). PD-weighted images, acquired with a long repetition time (TR) and a relatively short echo time (TE), are compared to both T2-weighted and fluid-attenuated inversion recovery (FLAIR) images. For best detection sensitivity of radiological HOD, an infratentorial axial T2-weighted sequence of the brainstem is included as a gold standard with the following parameters: matrix size 448 × 358, FOV 240 × 240 mm^2^, TE 116 ms, TR 4,400 ms, refocusing angle 130°, 20 axial slices, slice thickness 2 mm, and slice gap 0.2 mm. PD- and T2-weighted images are recorded simultaneously via a double-echo turbo spin echo sequence (TE 12 and 96 ms) with the following parameters: matrix size 384 × 384, FOV 240 × 240 mm^2^, TR 4,500 ms, refocusing angle 130°, 25 axial slices, slice thickness 2 mm, and slice gap 0.5 mm. In correspondence with the local clinical routine protocol, FLAIR images covering the entire brain are acquired with a matrix size of 320 × 224, FOV 220 × 193 mm^2^, TR 8,500 ms, TE 81 ms, TI (inversion time) 2,440 ms, refocusing angle 150°, 30 axial slices, slice thickness 4 mm, and slice gap 0.4 mm.

The DTI data are acquired using a novel sequence dubbed HASE-EPI sequence, as described in the literature (23). In comparison to commonly used single- and twice-refocused spin-echo EPI sequences, the HASE-EPI sequence allows for a slightly improved signal-to-noise ratio (SNR) due to the use of diffusion model independent of spatial resolution (thus shortened TE, especially for large matrix-size). The increased SNR improves the quality and quantity of the reconstructed fiber tracts. All DTI data are acquired with an isotropic resolution of 2 mm using the following parameters: FOV 256 × 256 mm^2^, matrix-size 128 × 128, 72 interleaved axial slices, slice thickness 2 mm, no inter-slice gap, TR 7,200 ms, TE 60 ms, echo-spacing 0.6 ms, bandwidth 1,953 Hz/pixel, partial Fourier encoding 6/8, parallel imaging (GRAPPA) with acceleration factor 2, 60 different diffusion weighting gradient (DWG) directions (*b*-value 1,000 s/mm^2^), and five pairs of reference (b0) volumes. The choice of directions is based on the full-sphere sampling of symmetrically distributed DWG directions. All imaging sequences used in this study are tested in pilot runs on healthy subjects prior to the start of the study (Figure 6).

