### Primary Endpoint

The primary endpoint of the study is the presence of radiological HOD on T2-weighted images at the time of follow-up 8 months after the index event. The presence of radiological HOD is reviewed and validated by two experts in the field, including at least one specialist in radiology with additional neuroradiology specialty, on the basis of the brain MRI with T2-weighted sequences. The radiological diagnosis of HOD is established in consensus if a new-appearing, circumscribed hyperintensity of the ION is present on T2-weighted or FLAIR imaging, optionally accompanied by hypertrophy of the ION (4, 8, 9).

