### Secondary Endpoints

Secondary endpoint values are the radiological incidence of HOD at 4 months after the index event, recorded as the main target value. Further secondary endpoints are the presence of HOD-specific symptoms in the clinical exam at follow-up and the impact of HOD development on disability outcome (mRS). The PD-weighted images of all patients will be reviewed by three blinded raters with a specialization in neuroradiology and rated for their quality of HOD identification in comparison to simultaneously acquired T2-weighted images. The DTI images will be analyzed for each individual patient with respect to lesion location within the fiber tracts of the GMT, thinning of fiber tract volume, and quantitative imaging parameters such as mean diffusivity and fractional anisotropy and will be reviewed.

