As a secondary study goal, quantitative imaging data acquired from the study cohort is utilized to provide insight into the complex brainstem connectivity. It can be assumed that the dentato-thalamo-cortical pathways behind HOD development are involved in other higher brain functions as well, as observed in the cerebellar mutism syndrome after posterior fossa surgery (3). Prior studies already applied structural and diffusion MRI data on the ION complex, and successfully tracked connections of the ventrolateral (parvocellular) subregions of the RN to the ION (24). The DTI fiber tractography is thus promising to illustrate the chronological course of fiber tract degeneration in HOD and associate the anatomical lesions from routine T2-weighted MR images to the respective fiber tract injury. Hereby, lesion areas most vulnerable for HOD development can be identified and a comparison of fiber tract volumes between symptomatic and asymptomatic HOD could be undertaken.

The HOD is not a common radiological diagnosis, and changes in conventional T2-weighted images may often be too subtle for a confident diagnosis. This study aims to provide the clinical radiologist with a more sensitive and specific sequence to confirm the suspicion of HOD: double-echo PD-weighted images with long TR are available on most clinical MR-scanners and are hypothesized to generate more contrast in the brainstem, allowing for a more certain and hereby more common diagnosis.

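### HOD is diagnosed only on T2 or FLAIR, so PD-weighted imaging cannot be shown more sensitive or specific than conventional T2; the T2 comparator also changes between sections

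*Protocol article*

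**What the plan says.** All places are in the Protocol article.

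**How HOD is established.** Primary Endpoint: "The primary endpoint of the study is the presence of radiological HOD on T2-weighted images". The diagnosis is made in consensus by two experts if a new "circumscribed hyperintensity of the ION is present on T2-weighted or FLAIR imaging". PD does not enter the definition. Study Outcomes adds that "an infratentorial axial T2-weighted sequence of the brainstem is included as a gold standard" (TE 116 ms, slice gap 0.2 mm).

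**What PD is meant to achieve.** The Introduction hypothesises that double-echo imaging (T2 plus PD) detects HOD better than conventional T2. The Discussion says that T2 changes can be too faint for a firm diagnosis, and then: "This study aims to provide the clinical radiologist with a more sensitive and specific sequence to confirm the suspicion of HOD".

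**What PD is compared with.**
- Design, secondary target (b): "to analyze the best detectability of radiological HOD in comparison to conventional T2-weighted sequences".
- Study Outcomes: PD images "are compared to both T2-weighted and fluid-attenuated inversion recovery (FLAIR) images", without saying which T2.
- Secondary Endpoints: three blinded raters review the PD images, which are "rated for their quality of HOD identification in comparison to simultaneously acquired T2-weighted images". That T2 is the second echo of the double-echo scan: "PD- and T2-weighted images are recorded simultaneously via a double-echo turbo spin echo sequence (TE 12 and 96 ms", slice gap 0.5 mm.

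**The concern.** The truth about HOD and the method that PD has to beat come from the same image contrast. The article holds that T2 may miss or blur the sign, yet it lets T2 (with FLAIR) decide who has HOD. The patients in whom PD would prove its worth, those whose HOD shows on PD but not on T2 or FLAIR, are the ones the definition leaves out.

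The changing comparator adds to this. Conventional T2, an unspecified T2 together with FLAIR, and the simultaneously acquired T2 are different yardsticks, and a result against one does not carry over to another.

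At stake is the message to radiologists in the Discussion. It is a claim about sensitivity and specificity that the planned data, read under the planned definition, cannot support.

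**Working it through.** **The plan's own figure.** The only precision figure in the article concerns the primary endpoint: 30 cases in 100 give 95% Clopper-Pearson limits of 0.21 and 0.40. Recomputed, the lower limit is the 2.5% quantile of Beta(30, 71) = 0.2124 and the upper limit is the 97.5% quantile of Beta(31, 70) = 0.3998. The figure is reproduced. No figure is given for PD versus T2.

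**Step 1: logic, no assumed numbers.** Let R be HOD status under Primary Endpoint (T2 or FLAIR consensus). PD's sensitivity is the share of R-positive patients who are PD-positive; its specificity is the share of R-negative patients who are PD-negative. A patient with true HOD seen only on PD is R-negative, so this patient
- does not enter the sensitivity at all, and
- counts as a false positive in the specificity.

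Against the conventional T2 read that sets the reference, PD can at best tie.

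**Step 2: illustration of size.** Inputs: n = 100 (Sample Size); 20 T2-positive patients (the 20% hypothesis in the Discussion). Assumptions: PD finds every true case without error; T2 gives no false positives; FLAIR adds no cases; T2's true sensitivity s runs from 100% to 70%.

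True cases = 20/s. PD-only cases = 20/s − 20. Apparent PD specificity = (80 − PD-only cases)/80.

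| True T2 sensitivity (assumed) | True HOD | PD-only, true | Apparent PD sensitivity | Apparent PD specificity |
|---|---|---|---|---|
| 100% | 20.0 | 0 | 100% | 100% |
| 90% | 22.2 | 2.2 | 100% | 97.2% |
| 80% | 25.0 | 5.0 | 100% | 93.8% |
| 70% | 28.6 | 8.6 | 100% | 89.3% |

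The more cases T2 misses, the worse a perfect PD sequence looks.

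**Step 3: the comparison that PD can win.** If PD and the double-echo T2 (TE 96 ms) are both judged against the dedicated T2 (TE 116 ms), neither is its own reference and PD can come out ahead. With about 20 reference-positive patients and one read per patient, the two-sided exact McNemar p-value when all b discordant pairs favour PD is 2 × 0.5^b. For b = 5 it is 0.0625 and for b = 6 it is 0.031. At the 0.05 level in Data Analysis (two-sided assumed), at least 6 of 20 patients, 30 percentage points, would have to differ, all in PD's favour.

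**The case against.** A reader might infer that T2 is test and reference in every comparison, that it scores 100% on both measures by construction, and that PD can never win. The documents do not support this, for three reasons.

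- Secondary Endpoints compares PD with the double-echo T2, while the gold standard is a separate acquisition with another echo time, matrix and gap.
- The reference is a two-expert consensus that may also rest on FLAIR. A case positive only on FLAIR, or a sign that a blinded rater overlooks, would be a T2 miss. T2 is perfect only if the same read serves as test and reference, and no section says so.
- The stated endpoint is a quality rating. No accuracy table against T2 is described, and better rated visibility can be shown without any reference.

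A reader might also infer that a truly better PD sequence would appear about 5 points worse on both measures. Assume 20 true cases, T2 sensitivity 80%, PD sensitivity 95%, no true false positives and independent errors. PD then scores 15.2/16 = 95% and 80.2/84 = 95.5%. If PD instead finds every T2-positive case, it scores 16/16 = 100% and 81/84 = 96.4%. The sensitivity deficit comes from the independence assumption, which is doubtful for two contrasts of the same olive.

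It is also fair that the accuracy wording stands only in the Discussion, that the Introduction speaks of double-echo imaging rather than PD alone, and that reading order and test choice may sit in the full protocol.

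All of this stands, and it narrows the point without removing it. A quality rating does not establish sensitivity or specificity. Adding PD to T2 does not change the definition of a case. Under none of these readings can HOD seen only on PD be credited as HOD. The conflict lies in what the article states, not in detail it leaves out.

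**Conclusion.** The point holds in a limited form. Because HOD is set on T2 or FLAIR and no other reference is stated, the study cannot show PD to be more sensitive or specific than conventional T2, which is what the Introduction, Design and Discussion intend. This follows from the definition alone. Its size depends on how much HOD T2 and FLAIR really miss, which the documents do not say; in the illustration, a perfect PD sequence loses 2.8 to 10.7 points of apparent specificity for a true T2 sensitivity of 90% to 70%, and nothing if T2 misses no case.

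PD can still be shown better than the simultaneously acquired T2 on rated quality. The plan does not rule out every favourable result for PD, nor does it fix a deficit of given size.

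The T2 comparator does differ between Design, Study Outcomes and Secondary Endpoints and should be settled.

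Severity is moderate: this is a secondary target of an exploratory study, and the primary endpoint and the sample size are unaffected.

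**What to change.** Name the simultaneously acquired T2 as the one primary comparator in Design, Study Outcomes and Secondary Endpoints, with the dedicated T2 and FLAIR as secondary comparators. Then choose one of two routes.

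(a) **Keep the accuracy aim.** The same three blinded raters read the 4-month PD images and the 4-month T2 images separately. The 8-month consensus under Primary Endpoint is the reference for both, and the reads are compared as pairs. An early detection on PD alone that is later confirmed then counts in favour of PD.

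(b) **Keep the quality rating.** Limit the conclusion to rated detectability, reader confidence and agreement, and remove the claim of better sensitivity and specificity from the Discussion.

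Cost: changes of wording and, mainly under (a), some extra reading time; no further scans. Under (a), HOD that arises between the two visits counts as a miss for both sequences alike. The reference still relies on T2/FLAIR contrast, so HOD that never shows there remains uncredited. With about 20 cases expected, the paired comparison will be imprecise and should be reported with its confidence interval.
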